## Abstract

**Background:**

Frequent rehospitalisations and poorer survival chances in heart failure (HF) patients may partly be explained by poor medication adherence. There are multiple medication-related reasons for suboptimal adherence, but psychological reasons may also be important. A novel TELEmonitoring device may improve MEDication adherence in HF patients (TELEMED-HF). TELEMED-HF is a randomized, controlled clinical intervention trial designed to examine (1) the efficacy and cost-efficiency of an electronic medication adherence support system in improving and monitoring HF patients' medication adherence; (2) the effect of medication adherence on hospitalizations and health care consumption; as well as on (3) clinical characteristics, and Quality of Life (QoL); and (4) clinical, sociodemographic, and psychological determinants of medication adherence.

**Methods/Design:**

Consecutive patients with chronic, systolic HF presenting to the outpatient clinic of the TweeSteden Hospital, The Netherlands, will be approached for study participation and randomly assigned (1:1) following blocked randomization procedures to the intervention (n = 200) or usual care arm (n = 200). Patients in the intervention arm use the medication support device for six months in addition to usual care. Post-intervention, patients return to usual care only and all patients participate in four follow-up occasions over 12 months. Primary endpoints comprise objective and subjective medication adherence, healthcare consumption, number of hospitalizations, and cost-effectiveness. Secondary endpoints include disease severity, physical functioning, and QoL.

**Discussion:**

The TELEMED-HF study will provide us a comprehensive understanding of medication adherence in HF patients, and will show whether telemonitoring is effective and cost-efficient in improving adherence and preventing hospitalization in HF patients.

**Trial registration number:**

NCT01347528.

## Background

The prevalence of symptomatic heart failure (HF) is rapidly growing due to the aging of the population, successful treatment of myocardial infarction, and increased survival after an acute cardiac event [1,2]. The more frequent need for rehospitalisations and poorer survival chances in the chronic HF population are associated with major healthcare costs. For instance, almost 390 million Euros were spent on HF care in the Netherlands in 2005, and it is expected that these costs increase during the following decades [3].

Pharmacological treatment of HF typically consists of a combination of ≥4 different types of medication [4]. A major problem in HF management is poor medication adherence with rates varying from 10% to 99% [5]. Poor adherence to treatment may to a great extent explain frequent readmissions in HF patients [5], and is associated with increased morbidity and mortality [6]. A recent longitudinal study showed that medication adherence rates above 88% were associated with a reduced number of rehospitalisations and mortality rates compared to non-adherent patients [7]. In this study, objective medication adherence was measured using an electronic chip in the medication cap (*"Medication Event Monitoring"*) that records each moment the cap is removed from the medication bottle [7]. Hence, improving medication adherence may enhance cardiac prognosis, reduce the number of HF-related hospital readmissions, improve quality of life (QoL), increase survival, and reduce healthcare costs [8].

A novel tool to improve patient adherence is home telemonitoring, permitting remote patient monitoring, either by structured telephone support [9], or using telecare devices in conjunction with a telecommunication system that electronically transfers patient data [10]. Two meta-analyses have shown promising results concerning the effect of telemonitoring on improving clinical outcomes in HF patients, i.e. reducing cardiac-related hospital re-admissions and all-cause mortality by nearly one fifth, and reducing healthcare costs while improving QoL [11,12]. Only one small study tried to improve medication adherence using a specific adherence device (i.e. a medication box transferring data to an electronic record), and found that this device improved patients' compliance [10]. Most studies examining the efficacy of home telemonitoring in HF patients were either based on small samples, were time-consuming due to extensive telephone support, or did not investigate the effect of telemonitoring on longer term outcomes, or the clinical course of HF [12]. A few major randomized controlled clinical trials did use a prospective design [13,14], such as TIM-HF with a long-term follow-up of 21 months [13]. However, these trials primarily focused on improving clinical outcomes instead of improving medication adherent behavior in HF patients.

When trying to improve patients' adherence, it is important to examine potential adherence modifiers from a multidimensional perspective. Disease characteristics, regimen related factors (e.g. polypharmacy), and medication side-effects may cause people not to take their medication [15,16]. Psychosocial and socio-economic factors, such as social support, and patient-related factors, such as self-care behavior, motivation, beliefs in medication, mood, cognitive dysfunction, and personality may also affect medication adherence in HF patients [16]. Previous studies on clinical and psychosocial factors that may affect medication adherence in HF failed to find determinants of adherence [17,18]. However, these were all drug trials in which adherence was around 90%, which is not representative of the HF population in general, in which adherence rates are evidently lower.

In summary, evidence suggests that medication adherence in chronic HF patients is poor, and that it remains unclear which method(s) may be effective in improving medication adherence, ultimately improving the patient's prognosis and QoL. While some studies aimed to improve medication adherence in HF patients, the majority of the devices only recorded adherence, such as "*Medication Event Monitoring" *[7]. In the present study, the effectiveness of a novel Medication Adherence Support System (MASS) to improve medication adherence will be investigated. The MASS supplies all pills put together in one or two small bags at specified times using pharmacy-prepared medication rolls. This makes the intervention especially suitable for chronic HF patients, who are mostly elderly, care dependent, and often receive multiple different types of medication. MASS not only records adherence, but is also designed to train medication adherent behavior, and is therefore a behavior-based intervention.

### Study objectives

The primary study objectives are to (i_a_) test the efficacy and cost-efficiency of the MASS (in addition to usual care) in improving adherence as compared to usual care alone (i.e. three visits to the HF nurse); and to (i_b_) investigate the effect of medication adherence on hospitalizations and health care consumption in HF patients.

The secondary objectives are to (ii_a_) determine the effect of medication adherence on clinical characteristics (i.e., measures of disease severity, physical functioning, cognitive function), and QoL; and to (ii_b_) identify clinical, sociodemographic, and psychological determinants of subjective and objective medication adherence, while examining their role in modulating adherence and the effect of the MASS.

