All patients will return to the HF outpatient clinic with a three-monthly frequency, meaning that in total three usual care visits are included in the intervention period. After the intervention period, all patients will continue to receive usual care, and will participate in four follow-up occasions at 9 (T2), 12 (T3), 15 (T4), and 18 months (T5) post-baseline that coincide with the regular three-monthly clinic appointments.

Every six months (i.e. at baseline (T0), at the end of the intervention (T1), and at 6 (T3) and 12 (T5) months thereafter), the following activities will take place in both study conditions: (i) a blood draw assessment of biochemical variables; (ii) a six-minute walk test; (iii) a NYHA functional class determination following standardized protocol; and (iv) an echocardiography to determine LVEF (%). The follow-up at 3 and 9 months will consist of a telephone call, only requesting information on healthcare consumption and adherence. The timeline of the study design is demonstrated in Figure 1.

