The main secondary study parameters include QoL, disease severity (NYHA functional class determination following standardized protocol; LVEF using echocardiography), and exercise capacity (six-minute walk test; see also Table 1). Other secondary variables are designed to determine whether randomization was successful, to assess their potentially moderating influence on adherence, and to generate risk profiles of patients who may or may not benefit from the intervention (see Table 1). These include: (1) psychological and sociodemographic variables; i.e. Type D personality, depression, anxiety, socio-economic status, age, gender, beliefs in medication, self-care behavior, and cognitive function; and (2) clinical variables; i.e., self-reported medication side effects; time since HF diagnosis; HF etiology; previous cardiac events (MI), previous cardiac procedures (PCI, CABG), previous cardiac devices (ICD, pacemaker), number of hospitalizations for HF; blood pressure; cholesterol; triglycerides; diabetes; atrial fibrillation; comorbidities; cardiac medication, other medication (including psychotropic medication); C-reactive protein; NT-pro-BNP; parameters measured in standard clinical practice (including liver function (ACAT, ALAT, Gamma GT), hemoglobin, hematocrit, leukocytes, and kidney function (urea and creatinine).

All endpoints will be assessed with standardized and validated measures shown to have good psychometric properties, usual care laboratory tests, physical examinations, and pharmacy refill records (Table 1).

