### Statistical analysis

This trial is designed to show whether the MASS device is effective in improving medication adherence in a chronic HF population compared to usual care only. Descriptive statistics (frequencies, means (±SD) will be calculated stratified by experimental group (intervention vs. usual care). T-tests for continuous variables and Chi-square tests for categorical variables will enable us to compare baseline values for both groups to formally test the successfulness of the randomization procedure. We will examine the effectiveness of the intervention by using the intention-to-treat principle, with the inclusion of all randomized participants in the statistical analyses regardless of whether they completed the intervention or the follow-up measurements. Missing data will be imputed using regression imputation techniques. The equality of subjective and objective adherence will be assessed by means of Intraclass correlation and Cohen's measure for agreement, the Kappa statistic, depending on the measure of adherence. Repeated measures analysis of covariance will be used to assess differences between the intervention and control group with respect to changes in adherence over the six-month intervention period, and to assess long-term effects (up to one year post-intervention) of the intervention on medication adherence, while taking potential confounders into account. To determine whether the time to hospitalization is longer for patients using the MASS device compared with patients in the control group, the log-rank test for comparison of Kaplan-Meier curves will be used. In addition, Cox proportional hazards regression modeling will be used to determine whether the usage of the MASS device predicts time to the first event (i.e. hospitalization due to HF or cardiac-related death). Multivariate regression analyses will be used to assess which psychological, clinical, demographic, and/or medication-related determinants predict adherence (with the percentage of adherence as dependent variable) in chronic HF patients and moderate the effects of the MASS device on patient adherence. The influence of potential effect modifiers will be examined by means of interaction terms.

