## Discussion

The TELEMED-HF study is designed to test the efficacy and cost-efficiency of an innovative telemonitoring solution, the MASS device, in improving medication adherence as compared to usual care alone in a large group of HF patients. Currently, a few major clinical trials have used strategies consisting of daily telemonitoring of symptoms and health behaviors in HF patients [13,14]. However, the TELEMED-HF study is the first trial that primarily focuses on improving medication adherence by recording adherence, dispensing all prescribed medication in the right dosage at the specified times, reminding patients to take their medicines, and collecting information about non-adherence from the MASS device and responding to it. While we have chosen for a commercially available telemonitoring device, the study is designed to test its concept rather than the product itself, resembling the Tele-HF study that investigated a commercially available system on health behaviors in HF patients [23].

As the MASS device is expected to train adherent behavior, it can be considered as a behavior-based intervention. To date, most studies did not examine the effect of telemonitoring on longer term outcomes past 6 months, nor the clinical course of HF [12]. This RCT is therefore designed to determine the effect of medication adherence on the clinical state, disease progression, health care consumption, and QoL with a follow-up period of one year. We will further examine the correspondence between objectively and subjectively assessed medication adherence. Finally, our aim is to identify psychosocial and clinical determinants of medication adherence, and their role in modulating adherence and the effect of the telemonitoring device.

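### The objective for quality of life, function and disease severity names adherence, which is not randomised, as the exposure, and the article specifies no comparison of these endpoints between the arms.

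*Protocol article*

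**What the plan says.** Objective ii_a in Study objectives is to "determine the effect of medication adherence on clinical characteristics", by which it means severity of disease and physical and cognitive function, and on quality of life. The abstract's aim 3 has the same structure, and the Discussion repeats it: "This RCT is therefore designed to determine the effect of medication adherence on the clinical state, disease progression, health care consumption, and QoL".

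The outcomes concerned are declared secondary endpoints. Study endpoints states: "The main secondary study parameters include QoL, disease severity (NYHA functional class determination following standardized protocol; LVEF using echocardiography), and exercise capacity", the last measured by the six-minute walk test. The abstract agrees: "Secondary endpoints include disease severity, physical functioning, and QoL".

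Table 1 schedules KCCQ, the walk test, NYHA and LVEF at T0, T1, T3 and T5. For the walk test, NYHA and LVEF, the section on study procedures adds that "the following activities will take place in both study conditions".

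For the analysis by arm, the Statistical analysis section says: "Repeated measures analysis of covariance will be used to assess differences between the intervention and control group with respect to changes in adherence". It adds a log-rank test and a Cox model for time to hospitalisation or first event. It names no model for the four secondary endpoints.

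**The concern.** Randomisation allocates the device, not adherence. Adherence is observed after randomisation and is shaped by the patient's condition. A patient who deteriorates may take fewer doses and also score worse on KCCQ, walk less far and move up a NYHA class, without the missed doses having caused any of this. An objective worded as the effect of adherence therefore asks a question that randomisation does not protect.

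The protected question is whether being given MASS changes quality of life, function or disease severity. The trial schedules the data to answer it, but no stated objective asks it of these endpoints. An analysis plan written faithfully to ii_a could regress the endpoints on adherence and present the coefficient as an effect found in a randomised trial.

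**Working it through.** **1. Exposure named in each objective (Study objectives).**
- i_a: MASS plus usual care against usual care alone. Randomised.
- i_b: adherence, for hospitalisation and healthcare consumption. Not randomised.
- ii_a: adherence, for disease severity, function, cognition and quality of life. Not randomised.

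Objective i_a shows that the authors name the randomised contrast when they intend it. Statistical power analysis confirms that adherence is meant as an exposure elsewhere, because the trial is sized on a Cox model with adherence as the predictor.

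**2. Is adherence confounded on the article's own account?** Yes. The Background lists disease characteristics, side-effects, mood, cognitive dysfunction and personality as possible influences on adherence. Several of these plausibly also affect KCCQ, walking distance and NYHA class. Objective ii_b is devoted to finding such determinants.

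**3. Analyses named in Statistical analysis, by outcome.**

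| Outcome | Named analysis | Contrast |
|---|---|---|
| Adherence | Repeated measures ANCOVA | Arm |
| Time to hospitalisation | Log-rank | Arm |
| Time to first event | Cox | Arm (MASS use) |
| Percentage adherence | Multivariate regression with interactions | Determinants; moderation of the MASS effect |
| KCCQ, six-minute walk, NYHA, LVEF | None named | None named |

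The section also has baseline comparisons by arm and an agreement analysis of subjective and objective adherence. Neither estimates an effect on the four endpoints.

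**4. What an arm comparison could detect.** The article gives no figure for these endpoints, so there is none to reproduce. For a continuous endpoint, two-sided 0.05 and 80% power, the detectable standardised difference is (1.960 + 0.842) × √(2/n), with n per arm.
- n = 200 (abstract and eligibility section): 2.802 × √(2/200) = 0.28 SD.
- n = 192 (480 included, less 19.9% attrition: 480 × 0.801 = 384): 0.29 SD.
- n = 160 (400 less 19.9%: 400 × 0.801 = 320): 0.31 SD.
- n = 200 adjusted for T0, assuming a T0–T1 correlation of 0.6: 0.28 × √(1 − 0.36) = 0.22 SD.

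The article gives no SD for KCCQ or the walk test, so these cannot be put into natural units.

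**5. Direction of the bias, by simulation (assumed inputs).** The set-up is 400 patients, MASS raising adherence by 0.3 SD, and no effect of adherence or MASS on KCCQ. Severity is half baseline and half worsening after T0. It is correlated −0.2 to −0.4 with adherence and −0.4 to −0.6 with KCCQ. With T0 KCCQ adjusted for and 2,000 trials per setting:
- the adherence coefficient was significant at 0.05 in 31% to 98% of trials (59% to 88% where the adherence correlation is −0.3);
- the arm coefficient was significant in about 5% to 6%, the nominal level within simulation error.

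None of these correlations comes from the article. The result shows that an adherence regression can signal an effect where there is none, while the arm comparison keeps its error rate. It does not estimate the bias in this trial.

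**The case against.** The strongest case on the other side has four parts.

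- **Silence cuts both ways.** The article names no regression of these endpoints on adherence either. A reader might infer that the trial will report a confounded association and can give no randomised answer. The article does not support that: it plans no such regression, and the data for an arm comparison are scheduled. This stands.
- **The same wording did not prevent arm comparisons elsewhere.** Objective i_b also speaks of the effect of adherence, yet time to hospitalisation is compared by arm, and Study endpoints says the TiC-P allows healthcare consumption to be compared between the groups. This stands as evidence that ii_a's wording does not exclude an arm comparison. It does not make ii_a ask for one.
- **General text could cover it.** The intention-to-treat sentence on effectiveness is not limited to adherence, Study design says secondary outcomes are evaluated before and after the intervention, and the full protocol or analysis plan, not shown here, may name a model. All true, so the absence of a model is not in itself the finding. What remains is an objective that names the wrong exposure, and a later plan would take its lead from that objective.
- **The simulation restates its assumptions.** It adjusts only for T0 KCCQ, although the trial records NT-proBNP, comorbidities, depression and cognition. This stands, so the rates are illustrative only.

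Studying how adherence relates to outcome is also a legitimate aim, and the point is not that it should be dropped.

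**Conclusion.** The point holds in a limited form. Objective ii_a, repeated in the abstract and the Discussion, words a non-randomised relation as an effect. For KCCQ, six-minute walk, NYHA and LVEF, the article commits to no comparison that uses the randomisation. It permits one without specifying it. It would be wrong to conclude that the trial cannot say whether MASS changes these outcomes.

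The conclusion rests on the wording of the objectives, the list of named analyses and the article's own account of what drives adherence. It does not depend on any calculation. The size of the confounding is unknown. The detectable differences of 0.28 to 0.31 SD without adjustment describe what the arm comparison could show and are not evidence of a defect. Because the endpoints are secondary and the repair is easy, this is a change that should be made rather than a threat to the trial.

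**What to change.** - Restate ii_a so that MASS versus usual care is the main contrast for KCCQ, six-minute walk, NYHA and LVEF. Align the abstract's aim 3 and the Discussion.
- Add to Statistical analysis an intention-to-treat comparison of the arms at T1, then at T3 and T5, adjusted for the T0 value of the same measure, with an ordinal model for NYHA.
- Keep the adherence-outcome analyses as a separate aim, and report them as observational associations with the adjustment variables stated.

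The cost is the rewording of one objective and a few extra models on data already scheduled. No visits, patients or measurements are added.

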## Study design

The TELEMED-HF study is a Dutch, open, prospective, randomized, controlled clinical intervention trial (RCT) designed to improve medication adherence using a telemonitoring solution in a large group of HF patients. Primary and secondary outcomes will be evaluated pre- and post-intervention with a follow-up of 12 months. The trial has been registered at http://www.ClinicalTrials.gov (NCT01347528). TELEMED-HF is expected to report its first results in autumn 2013.

### Study population and eligibility criteria

Consecutive patients with a diagnosis of chronic, systolic HF presenting to the HF outpatient clinic of the TweeSteden hospital Tilburg/Waalwijk, The Netherlands, will be approached for study participation and randomized to the intervention arm (n = 200) or usual care arm (n = 200) at inclusion. Eligible patients must (a) have a diagnosis of stable HF, (b) New York Heart Association (NYHA) functional class II-III, with a decreased pump function (left ventricular ejection fraction (LVEF) < 40%), (c) titrated to the most optimal doses of ACE-inhibitor or angiotensin receptor blocker (ARB), and beta-blocker, (d) receiving stable doses of at least three HF medications for one month with no plans to add or adjust HF medications or titrate further in the immediate future, and (e) providing written informed consent.

Exclusion criteria are: (a) age < 50 years, (b) diastolic HF (intact pump function), (c) either myocardial infarction, or invasive treatment (percutaneous coronary intervention (PCI) or coronary artery bypass grafting (CABG)), or hospitalization within one month prior to inclusion, (d) participation in another clinical trial, (e) life-threatening co-morbid conditions (e.g., cancer), (f) diminished mental capacities (suspected serious cognitive decline will be confirmed by a Mini Mental State Examination (MMSE score ≤24 [19])), (g) a history of psychiatric disorders apart from affective disorders (depression and anxiety disorders), (h) significant sight and/or hearing impairment, and (i) insufficient knowledge of the Dutch language.

